## Abstract

**Method::**

This study will be an investigator-initiated, assessor-blinded, comparative, superiority pilot randomized controlled trial. A total of 30 patients with dry eye will be randomly assigned to the experimental or the control group in equal proportion. For the experimental group, the BMA will be applied to both sides of 5 acupoints including BL2, GB14, TE23, EX-HN5, and ST1. For the control group, conventional intradermal acupuncture will be applied to the same acupoints. The needles will be attached for 4 hours. Over 4 weeks, both the interventions will be performed 12 times in total. The primary outcome would be the ocular surface disease index. The secondary outcomes would be the visual analog scale for subjective symptoms, quality of life, Schirmer I test, and general assessment.

**Discussion::**

The findings of this study on the efficacy and safety of the BMA would be helpful for patients with dry eye in clinical practice. Further, these results would provide for the foundation of a large-scale BMA study.

## 1. Introduction

Dry eye syndrome is a lacrimal disease caused by insufficient secretion or excessive evaporation of tears, which leads to ocular surface damage, and accompanies irritating symptoms, including discomfort, foreign body sensation, or dryness of the patient’s eye.^[1]^ According to a report from the National Health Insurance Service of Korea in 2018, the prevalence of dry eye has steadily increased by 2.1% annually since the recent 5 years.^[2]^ Nowadays, dry eye can be aggravated by various environmental factors, which include excessive use of visual display terminals, increase in indoor stay, fine dust, or growing use of contact lenses.^[3–5]^ Although artificial tears, corticosteroid eye drops, cyclosporine, therapeutic contact lenses, protective glasses, and punctal occlusion have been suggested as treatments, they have several side effects and are not considered fundamental treatment options.^[6–9]^

In Korean medicine, acupuncture or herbal medication, which clear heat, nourish the yin and body fluid, or supplement the blood and qi, have been traditionally used for dry eye.^[10]^ Clinically, acupuncture has been considered the main Korean medicine treatment for dry eye. Hence, studies^[11–14]^ on the efficacy of acupuncture for dry eye have been steadily reported; however, these prior studies are mainly limited to case reports. Thus, a randomized controlled trial (RCT) is necessary to establish the evidence of acupuncture for dry eye.

Intradermal acupuncture (IDA) is a type of acupuncture commonly used for dry eye in clinical practice; however, related clinical studies are rare. Thus, we conducted preliminary studies on the efficacy and safety of IDA for dry eye. First, we searched RCTs on IDA for dry eye from domestic and foreign databases, and analyzed 4 eligible RCTs.^[15]^ Thereafter, we conducted a preliminary RCT (not published yet) comparing IDA with body acupuncture for dry eye. This study has suggested significant improvement of the ocular surface disease index (OSDI) in both interventions, no difference upon intergroup comparison, and safety of IDA.

This study assesses the efficacy and safety of a biodegradable microneedle acupuncture (BMA) for patients with dry eye compared to conventional IDA. Based on the results, this study aims to demonstrate the superiority of BMA for dry eye compared to conventional IDA.

## 2. Method

### 2.1. Study design

This study is designed as an investigator-initiated, parallel, superiority RCT. Patients with dry eye who voluntarily agree to this study would be screened using the necessary examinations and eligibility criteria. The suitable participant would be randomly allocated to the experimental group or the control group on visit 1. The participants allocated to the experimental group would be treated with the BMA. In contrast, the participants allocated to the control group would be treated with IDA. For 4 weeks, both the groups would be treated 3 times a week (total 12 times) by each intervention. Within 4 weeks from visit 1, the investigators would conduct the final assessment after treatment termination, and the trial would be completed.

### 2.2. Sample size and recruitment

The exact calculation of the number of participants for statistical analysis for this pilot study is challenging because owing to the few reports on BMA. The number of participants for a pilot study should be at least twelve people per group as suggested by a previous study.^[16]^ Considering a dropout rate of 20% owing to a total of 12 treatments for 4 weeks, this study requires fifteen participants per group. Thus, the total required participant number for this study is thirty.

Participants would be recruited via advertisements in a single hospital. If a patient desires to participate, investigators would detail the study. Then, the participant who voluntarily submits the written consent would be screened using the inclusion and exclusion criteria. If considered suitable, the participant would receive a unique participant number.

### 2.3. Participants

#### 2.3.1.
*Inclusion criteria*.

Participants should satisfy all the following criteria:

Male and female aged between 19 and 65 years.Patients with dry eye having typical symptoms, including pruritus, foreign body sensation, irritation, pain, dryness, blurry eye, dazzle, eye congestion, and excessive lacrimation, and whose OSDI score is more than 13.Less than 10 mm/5 min in the Schirmer I test.Those who voluntarily submit the written consent.

#### 2.3.2.
*Exclusion criteria*.

Patients who satisfy any criterion of the followings would not be able to participate:

Dry eye symptoms attributed to the eyelid or eyelashes.Eye irritation attributed to acute inflammation of the eyelid, eyeball, or ocular appendage.Skin diseases including Stevens–Johnson syndrome or pemphigoid.Vitamin A deficiency.Eyeball or ocular appendage injuries.Received operations via anterior chamber, including cataract or laser-assisted in situ keratomileusis, within recent 3 months.Having a difficulty in blinking owing to facial palsy.Received punctal plug or punctal occlusion.Used anti-inflammatory eye drops including cyclosporine, corticosteroids, or autologous serum eye drops recently within 2 weeks.Active ocular infections, including anterior uveitis or anterior blepharitis.Those who have ocular allergy or are undergoing treatments for allergic eye diseases.Those who have symptoms or are undergoing treatments for viral conjunctivitis.High intraocular pressure of more than 25 mm Hg or glaucoma of any eye.Taking systemic corticosteroids or immunosuppressants treatment.Pregnant, nursing women, or women planning pregnancy.Others considered ineligible by the investigators.

### 2.4.
*Randomization and allocation concealment*

Block randomization will be used to divide the participants into 2 groups. The randomization will be conducted by a statistical software (SAS; SAS Institute Inc., Cary, NC). Setting the block size as 4, total 30 people would be randomly allocated into 2 groups with the same possibility. Thus, 15 participants would be assigned to each group.

Allocation would be decided after screening. Investigators will open an opaque and sealed envelope, which contains the allocation result, in front of the suitable participant. The opened envelope will be stored separately.

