### 2.5. Blinding

This study is single-blind, which only blinds the assessor. Double-blinding is challenging for this study since the participants and investigators would be aware of the applied treatment. Moreover, the investigators who treat interventions cannot objectively assess the result. Thus, the assessor would be blinded to strengthen the objectivity of this study and reduce the bias of the investigators.

In order to ensure blinding, the roles of the investigators would be categorized into the assessor, clinical research coordinator, and therapist. The assessor would not be able to contact the participants except for the assessment time. An additional assessment form, which does not contain identifiable personal information, would be prepared for the assessor.

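### A single block size of 4 does not give the stated 15 per group in 30 participants, and it could make up to about 31% of allocations certain in advance to staff who know the size and keep a tally

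*Protocol article*

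**What the plan says.** Section 2.4 of the protocol article names the method: "Block randomization will be used to divide the participants into 2 groups". It then gives the setting: "Setting the block size as 4, total 30 people would be randomly allocated into 2 groups with the same possibility". From this it concludes: "Thus, 15 participants would be assigned to each group". No second block size, closing short block or stratification is mentioned. The abstract confirms equal allocation: "randomly assigned to the experimental or the control group in equal proportion".

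The figure of 15 per group comes from section 2.2. The starting point is "The number of participants for a pilot study should be at least twelve people per group as suggested by a previous study", followed by "Considering a dropout rate of 20% owing to a total of 12 treatments for 4 weeks, this study requires fifteen participants per group".

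The setting matters for predictability. Section 2.2 says "Participants would be recruited via advertisements in a single hospital", so there is apparently one sequence. Under section 2.4, investigators open sealed opaque envelopes after screening. Section 2.5 blinds only the assessor: "Double-blinding is challenging for this study since the participants and investigators would be aware of the applied treatment". Section 2.3.2 ends with an exclusion left to the investigators' judgement.

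**The concern.** Two things follow from using one block size of 4 for 30 participants.

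First, 30 is not a multiple of 4, so permuted blocks of 4 alone cannot guarantee equal groups. The article presents 15:15 as a consequence of the scheme, which it is not.

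Second, a small fixed block lets anyone who knows its size and remembers earlier allocations work out some of the later ones. Sealed opaque envelopes do not prevent this, because the inference uses past assignments and not the contents of the next envelope. A person who could foresee an assignment while judging eligibility, or while choosing when to randomize (section 2.8.2 allows visit 1 on the screening day or up to 7 days later), could influence who enters which arm. Blinding the assessor does not undo selection at entry. The primary outcome, the OSDI, is a questionnaire answered by participants who know their treatment, so sound allocation is one of the few protections left for the comparison.

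**Working it through.** **Inputs.** Total 30, block size 4, 1:1 allocation (section 2.4 and abstract); 12 per group and 20% dropout (section 2.2).

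**The plan's own sample size.** 12/(1 − 0.20) = 15 per group, 30 in total. This reproduces.

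**Group sizes.** 30/4 = 7.5. Seven complete blocks give 7 × 4 = 28 participants, split 14:14. The last two take the first two places of an eighth block. There are six equally likely orders of AABB:

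- ABAB, ABBA, BAAB and BABA start with one of each: 4/6, so P(15:15) = 2/3.
- AABB and BBAA start with two alike: 2/6, so P(16:14, either way round) = 1/3.

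**Cost of 16:14.** The variance of a difference in means is proportional to 1/n₁ + 1/n₂. The ratio to equal groups is (1/16 + 1/14)/(2/15) = 0.13393/0.13333 = 1.0045, an increase of 0.45%. At 20% dropout, an arm of 14 leaves an expected 14 × 0.8 = 11.2, just under the 12 that section 2.2 aims for.

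**Allocations certain in advance (block size known, tally kept).** An assignment is certain once one arm has used both its places in the current block.

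| Place in block | P(certain) |
|---|---|
| 1 | 0 |
| 2 | 0 |
| 3 | 1/3 (first two alike) |
| 4 | 1 |

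The sum is 4/3 per block. Over the list: 7 × 4/3 + 0 (the two leftover places) = 9.33 of 30, or 31.1%. If the list instead closes with a block of 2, its second place is also certain: 10.33 of 30, or 34.4%.

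**Best guess.** Always guessing the arm that is behind, and tossing a coin when the arms are level, gives an expected 17/6 = 2.833 correct per block of 4 and 0.5 + 2/3 = 1.167 in the two leftover places. (7 × 2.833 + 1.167)/30 = 21/30 = 70%, against 50% by chance. This needs only a running tally, not the block size.

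**Effect of mixed blocks, illustrated for a whole list of three 4s and three 6s.** 3 × 4 + 3 × 6 = 30, so 15:15 is guaranteed. A block of 6 has an expected 1.5 certain places and 4.1 correct guesses.

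- Sizes and order both known: (3 × 4/3 + 3 × 1.5)/30 = 8.5/30 = 28.3% certain.
- Set of sizes known, order hidden: about 11% certain (simulation of 60,000 lists, mean 3.28 of 30).
- Best-guess rate: (3 × 2.833 + 3 × 4.1)/30 = 20.8/30 = 69.3%.

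Hiding the order therefore lowers certainty but hardly changes the guess rate. Adding blocks of 2 would work against this: a list of 2, 2, 4, 4, 6, 6, 6 gives a guess rate of 69.9%, and 30.6% certain if sizes and order became known.

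**The case against.** The imbalance alone is minor. 15:15 is the most likely result under the text, and 16:14 changes neither the analysis nor, in practice, the precision. A closing block of 2 would make 15:15 certain, and a condensed article may have left that detail out. All of this stands, but the sentence as printed names one block size and draws a conclusion that this size does not support.

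On predictability, a reader might infer that recruiting staff do know about a third of allocations beforehand. The article does not establish that. It speaks only of investigators. Section 2.5 divides their roles into assessor, coordinator and therapist, and section 2.4 has opened envelopes stored separately. It does not say who screens, whether that person also sees allocations, or who was told the block size. The 31% is what a fully informed recruiter could know, not what any named role is shown to know.

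A reader might also infer that the block size was published while patients were still being enrolled. The article is dated 25 November 2022, and section 2.13 says that the trial is ongoing, with first enrolment on 6 July 2022. In a 30-patient trial with four weeks of treatment, enrolment could already have closed. The text does not settle this.

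Finally, the article's silence on who prepared and held the list is ordinary for a condensed report and is not counted here.

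**Conclusion.** The point holds in two parts of unequal certainty. It is certain that 15 per group does not follow from blocks of 4 in 30 participants: the chance of 16:14 is 1/3. This is an inconsistency of wording with negligible statistical cost. It does not make the sample size of 15 per group wrong, since that figure reproduces from section 2.2.

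The predictability is a real design weakness whose size is conditional. Up to 9.33 of 30 allocations (31%) are expected to be certain in advance if someone involved in recruitment or screening knows the block size, tracks a single unstratified sequence and sees past assignments. The documents make this possible (one site, unblinded investigators, a block size printed in the protocol) but do not show that it occurs. No actual selection is alleged. The matter deserves correction because the remedy is cheap, not because the result is shown to be compromised.

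**What to change.** **If places remain unassigned.** Complete the current block of 4. Then fill the remaining places with blocks of 4 and 6 in random order whose sizes sum to those remaining places, so that the total reaches 30 with 15:15. Do not disclose the sizes to site staff. Use a block of 2 only where the total requires it. After m completed blocks of 4, 30 − 4m places are left: 26, 22, 18, 14, 10 and 6 can all be made from 4s and 6s (for example 14 = 6 + 4 + 4), and only 2 needs a block of 2. The gain is in certainty: about 11% instead of 31% in the whole-list illustration with the order hidden. It will be smaller when few blocks remain, and the best-guess rate stays near 69%.

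**If the present list is kept or enrolment is complete.** Replace the concluding sentence of section 2.4 with a statement that each group will have 14 to 16 participants. If the list did close with a block of 2, say so. That guarantees 15:15, but certain allocations are then 34% if the sizes are known.

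**Cost.** A change of list needs a short amendment, new envelopes for the unused places and documented care when replacing a sequence mid-trial. Correcting the sentence costs nothing more than the edit. Neither needs extra patients.

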### 2.5. Blinding

This study is single-blind, which only blinds the assessor. Double-blinding is challenging for this study since the participants and investigators would be aware of the applied treatment. Moreover, the investigators who treat interventions cannot objectively assess the result. Thus, the assessor would be blinded to strengthen the objectivity of this study and reduce the bias of the investigators.

In order to ensure blinding, the roles of the investigators would be categorized into the assessor, clinical research coordinator, and therapist. The assessor would not be able to contact the participants except for the assessment time. An additional assessment form, which does not contain identifiable personal information, would be prepared for the assessor.

### 2.6. Interventions

#### 2.6.1.
*The experimental group*.

The experimental group would be treated using a disposable sterilized BMA (RMD-PN1; Raphas Co. Ltd., Seoul, Republic of Korea). The basic shape of BMA is the same as a microneedle patch. Five biodegradable hyaluronic acid microneedles are attached to a hydrocolloid film (Fig. 1). The specifications of the BMA are presented in Table 1. BMA would be applied to both sides of 5 acupoints, including BL2, GB14, TE23, EX-HN5, and ST1, by Korean medicine specialists or residents who have more than 3 years of clinical experience. Attached BMAs would be removed after 4 hours. For 4 weeks, the participants would receive the treatment 12 times in total.

**Table 1 T1:** Specifications of biodegradable microneedle acupuncture.

Model name	RMD-PN1
The length of needle (mm)	1.2
The thickness of needle (μm)	<80
Array spacing (mm)	>1.4
Total length (mm)	
Width	20
Length	24
Substrate film length (mm)	
Width	16
Length	16
Weight (mg)	124 ± 12

**Figure 1. F1:**
[figure not shown]
Structure of BMA. (A and B) Anterior side of the BMA. (C) Posterior side. The numbers in the figures indicate each component of the BMA; ①: microneedles, which are inserted into the skin; ②–④ constitute a sheet of substrate film; ②: microneedle-supporting film; ③: adhesive surface, which serves as adhesion to the skin; ④: adhesive surface protective film, which covers the posterior side of the adhesives; ⑤: release paper, which protects the adhesive surface and is separated before use. BMA = biodegradable microneedle acupuncture.

#### 2.6.2.
*The control group*.

Considering the intervention for the control group, IDA would be used with a disposable sterilized IDA needle (T-press needle DB130A; Dongbang Medical, Seongnam, Republic of Korea), also called “thumbtack needle.” A 0.18 mm × 1.0 mm-sized stainless-steel needle is attached to a small piece of paper plaster (Fig. 2). IDA would be applied to both sides of 5 acupoints, including BL2, GB14, TE23, EX-HN5, and ST1, by Korean medicine specialists or residents who have more than 3 years of clinical experience. Attached IDA needles would be removed after 4 hours. For 4 weeks, the participants would receive the treatment 12 times in total.

**Figure 2. F2:**
[figure not shown]
Conventional intradermal acupuncture needle. A small sterilized stainless steel thumbtack needle fixed on a square adhesive plaster. Ten pieces of needle are bundled in a transparent plastic baseplate. When using, take a piece off from the baseplate and attach it to the targeted acupoint.

### 2.7.
*Prohibited and permitted concomitant treatment*

During the trial, all kinds of concomitant treatments, including Korean medical therapy, would not permitted to both groups. The concomitant use of medications including anti-inflammatory eye drops, corticosteroids, or immunosuppressants would be prohibited. Participants who used such unauthorized medications would be dropped out from the study, and excluded from the final analysis.

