#### 2.9.3.
*Safety assessment*.

AE includes any unintended results that occurred even though the medical device was appropriately used according to the instructions. The expected AEs of the IDA are local pain from the treated area, local bleeding from the treated area, allergic reactions of the skin, infections, localized infection symptoms (redness, swelling, and/or local pain), nausea, vomiting, headache, and/or dizziness.^[22,23]^ For the BMA, redness on the treated area, skin irritation, and/or skin erosion are also expected in addition to the expected AEs of the IDA. Investigators would check and record the emergence of AEs on the CRF at each visit.

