#### 2.11.1.
*Criteria for discontinuing*.

Violating inclusion criteria or satisfying exclusion criteria.Emergence of serious AEs, or challenging in trial continuation due to AEs.A participant or his/her legal representative demands for discontinuing the trial owing to unsatisfactory therapeutic effect.Compliance with the trial is below 80%.Violations of the study protocol by investigators or participants.Withdrawal of participant’s agreement to the study.Loss to follow-up.During the treatment visits or the follow-up visit, the medications which can influence on the outcomes assessment were used without the investigators’ permission.Others considered inappropriate to proceed the trial by the investigators.

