#### 2.11.2.
*Criteria for exclusion from analysis*.

If a severe protocol violation occurs, the participant would be excluded from the final analysis, and the data would be analyzed using an intention-to-treat analysis. The followings are severe violations of the protocol:

Violations of the eligibility criteria.Used prohibited concomitant medications during the trial.The assessment for primary outcome was omitted at the beginning and/or end of the trial.The number of treatment did not exceed 80% of total scheduled treatments.

For minor violations, investigators would accurately record the degree of violation and its reason. Thereafter, an investigator, a statistician, and a monitor would comprehensively consider the influence on the trial when writing the outcome report. The data would be analyzed using a per-protocol analysis.

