## 3. Discussion

Many studies have introduced the superior therapeutic effect of acupuncture for dry eye than artificial teardrop.^[14,24]^ Furthermore, we concluded that IDA is effective for dry eye based on the RCTs that compared IDA and artificial teardrop in our prior literature review.^[15]^ BMA, a newly developed medical device, originated from the traditional IDA needle but resolved its shortcomings. Thus, this study aims to assess the superiority of BMA to the conventional IDA for dry eye by conducting a clinical trial.

IDA is a type of acupuncture that embeds a small needle in the skin for a long time, to stimulate the acupoints with prolonged weak stimulus. This therapy combined “shallow needling” among ancient needling techniques with “needle retention method,” which was described in the “Huangdi’s Internal Classic.”^[25]^ IDA has lesser pain than conventional body acupuncture, and it does not interrupt daily life or physical activity even though the needle is attached to the patient’s body. Using these features, many Korean medicine doctors have used IDA to treat diseases that require prolonged needle retention to the body surface, including obesity, ceasing smoking, nervous headache, stomachache, migraine, eye strain, dry eye, hypertension, asthma, or menstrual irregularity.^[26–29]^ However, the IDA needle can result in foreign body sensation to the patient if attached for too long, or provoke metal allergic symptoms, including skin inflammation and pruritus, owing to its material.

To overcome the limitation of the IDA needle, BMA used in this study was developed by the Raphas Co. Ltd. The material for the microneedle was changed from stainless steel to biodegradable macromolecule, hyaluronic acid. The safety of hyaluronic acid has been proved by its various applications to eye drops, dermal fillers, and moisturizer in cosmetics. The microneedles of the BMA made from hyaluronic acid completely decompose when inserted to the skin; therefore, they do not provoke allergic reactions in the skin compared to the metal needle.^[30]^ In addition, BMA minimized the risk of infection by gamma sterilization.

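### Sections 2.7 and 2.11.2 exclude randomised participants who use prohibited medication from the final analysis, under an intention-to-treat label and with no clear exception for treating an adverse event

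*Protocol article*

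**What the plan says.** Section 2.7 bars concomitant treatment in both groups and prohibits an open list of medications that includes corticosteroids, immunosuppressants and anti-inflammatory eye drops. It limits neither route nor reason for use. The consequence is: "Participants who used such unauthorized medications would be dropped out from the study, and excluded from the final analysis".

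Section 2.11.2 says that after a severe violation "the participant would be excluded from the final analysis, and the data would be analyzed using an intention-to-treat analysis". Its list of severe violations includes "Used prohibited concomitant medications during the trial" and, separately, "The assessment for primary outcome was omitted at the beginning and/or end of the trial".

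Section 2.11.1 covers stopping rather than analysis. One criterion is "Emergence of serious AEs, or challenging in trial continuation due to AEs". Another applies where "the medications which can influence on the outcomes assessment were used without the investigators", the sentence going on to refer to their permission.

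Section 2.9.3 expects skin allergy and infection with both devices; for BMA, "redness on the treated area, skin irritation, and/or skin erosion are also expected in addition to the expected AEs of the IDA". The Discussion says that the steel IDA needle can "provoke metal allergic symptoms, including skin inflammation and pruritus, owing to its material".

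**The concern.** Taking a prohibited drug during the trial happens after randomisation. Removing those who do so breaks the comparison that randomisation set up, whatever the analysis is called. Section 2.11.2 applies the intention-to-treat name in the very sentence that takes the participant out, so the name gives no reliable protection.

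The removal is more troubling if the allocated device can bring it about. The article expects skin reactions in both arms, with different profiles, and a reaction may need medication. If the drug chosen falls under the prohibition, the participant leaves follow-up and the analysis because of a treatment effect. Exclusions of that kind can differ between arms, and in a trial of 30 a few of them matter.

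**Working it through.** **The plan's own figure.** Section 2.2 takes 12 per group and allows 20% dropout: 12/(1 - 0.20) = 15 per group, 30 in total. This reproduces, and nothing here changes it. The allowance is 0.20 × 15 = 3 per arm.

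**The text side by side.**

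1. Randomisation comes before the first treatment (2.8.2), so any exclusion for medication used to treat a device reaction is post-randomisation.
2. Section 2.7 removes the user from both the study and the final analysis. Section 2.11.2 excludes on use alone, with no qualifier for reason or permission.
3. OSDI is measured at visits 1, 7 and 13 (2.9.1). A participant dropped before visit 13 has no end value, which is itself a severe violation in 2.11.2.
4. Section 2.11.2 also excludes anyone whose treatments do not exceed 80% of those scheduled: 0.80 × 12 = 9.6. Being dropped before the tenth session therefore meets that criterion as well.
5. The permission wording in 2.11.1 governs discontinuation. It does not appear in the 2.11.2 list.

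**Size of one case.** 1/15 = 6.7% of an arm; 1/30 = 3.3% of all randomised; 1/3 of the dropout allowance for an arm.

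**Effect on the arm mean.** Let m be the mean OSDI change of the other 14, and m + d the change of the participant concerned.

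- Mean with all 15: (14m + m + d)/15 = m + d/15.
- Mean after exclusion: m.
- Shift caused by exclusion: m - (m + d/15) = -d/15.

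The documents do not give d. Assumed values:

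| d (points) | Shift in arm mean |
|---|---|
| -20 | +1.33 |
| -10 | +0.67 |
| +10 | -0.67 |
| +20 | -1.33 |

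**How often.** The documents give no rate of prohibited-drug use for an adverse event. For an assumed rate p in an arm of 15, P(at least one) = 1 - (1 - p)^15, and P(three or more) is the binomial upper tail:

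| Assumed p | At least one | Three or more |
|---|---|---|
| 2% | 26% | 0.3% |
| 5% | 54% | 3.6% |
| 10% | 79% | 18% |

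These rates only show the scale; they are not estimates for this trial.

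**The case against.** **The fault is a garbled description of analysis sets, and the adverse-event angle is incidental.** Much of this stands. Section 2.11.2 names both intention-to-treat and per-protocol analyses, and the authors may have meant violators to leave only the latter. Repairing that section would remove most of the problem. But 2.7 separately excludes from the final analysis without qualification, so both sections need the change. This is a stated rule, not detail that an article leaves out.

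**There is room for an exception.** The word unauthorised in 2.7 and the permission wording in 2.11.1 may mean that medication an investigator allows does not trigger removal. That is why the point is the absence of a clear exception. A reader might infer that anyone treated for a reaction must be excluded, or that 2.7 and 2.11.1 flatly contradict each other; the text supports neither. Permission would not be a sound cure, though. Apart from the assessor, the investigators know the allocation (2.5), so membership of the analysis would rest on an unblinded decision.

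**Last observation carried forward (2.10.1) implies that some participants without a final value stay in.** That is a fair hint that a fuller set was intended. It does not settle the matter, because 2.11.2 excludes anyone lacking the end assessment of the primary outcome.

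**The step from reaction to prohibited drug is inferred.** This stands. No section says how a reaction would be treated, and many of the expected reactions would not obviously call for a named drug. Some affected participants might also stop under the adverse-event criterion in 2.11.1, although stopping need not mean exclusion from analysis.

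**It is a small pilot.** True, but the article states a superiority aim and intends the results to support a larger trial.

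**Conclusion.** The point holds. As written, 2.7 and 2.11.2 create post-randomisation exclusions for prohibited medication, and the intention-to-treat label does not prevent them. This rests on the text alone. Treatment of a device reaction is one plausible way in which the allocated treatment could cause such an exclusion; that part is inference.

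A reader might go further and infer that the rule favours BMA, because 2.9.3 lists more skin reactions for it. The documents do not support a direction: the Discussion attributes metal allergy and skin inflammation to the comparator needle and claims that BMA avoids allergic reactions. The sign of d is unknown as well.

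One case costs 6.7% of an arm and moves that arm's mean by -d/15, which is 0.67 to 1.33 points either way if d is assumed to be 10 to 20 points in size. Even at an assumed 10% rate, three or more cases in an arm have only an 18% chance. The plan should be amended because the rule is explicit and the repair is cheap, not because a large bias has been shown.

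**What to change.** Amend 2.7 and 2.11.2 so that:

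1. All randomised participants stay in the intention-to-treat analysis, whatever medication they used and whether or not it was authorised.
2. Use of medication does not end follow-up, and visit 13 is still done where the participant consents.
3. Use of prohibited medication leads to exclusion only from the per-protocol (sensitivity) analysis.
4. The reason for and dates of use are recorded on the CRF, and counts are reported by arm.

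How a reaction is treated remains a clinical decision.

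The cost is a short amendment to two sections and one extra entry beside the medication changes that 2.8.3 already has recorded. The sample size does not change. Enrolment has begun (2.13), so the follow-up rule can help only participants still in the trial, but the analysis-set rule can be settled for everyone before the data are analysed. The small downside is that some intention-to-treat outcomes may reflect the medication taken, which the per-protocol analysis will show.
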